### Data collection methods

Each household will receive a specific identification (ID) number tagged onto a colored metal plate placed on the upper front door of the house. Each inhabitant in the household will also receive a unique personal, three-digit ID number (village number/household number/person number). The latitude and longitude of each household will be recorded using a hand-held Global Positioning System (GPS) device. The GPS data will be downloaded to a computer for the creation of maps of the study villages and for a spatial analysis of epidemiological, entomological and economic data. Guidelines for the data collections will be developed during the pilot studies. All questionnaires and forms will be initially prepared in English and translated into a local language for data collection.

#### Epidemiological data collections

PCD of malaria cases at the health posts will be carried out throughout the trial using RDTs, and thin and thick blood smears for microscopic examination. We will recruit 24 data collectors (two data collectors per *kebele*) for a weekly household visit, 14 nurses (one nurse per *kebele*) for malaria diagnosis and treatment at the health posts and three field supervisors. Data collectors will be trained on questionnaire specifics, interviewing techniques and household visits. They will visit households weekly to help identify residents with fever, or a history of fever in the last 48 hours, to refer to the health posts and track information on LLINs’ use by household members during the night before the survey.

The research team and supervisors will make regular field visits for quality control of the work done at health posts. Each field supervisor will be responsible for 59 clusters, and will meet with data collectors and health workers at the health posts at least once a week. During these visits supervisors will check patient registration books, malaria surveillance forms and the availability of antimalarial commodities, and collect completed forms and blood slides and bring them back to the project’s office. Throughout the study period, all health posts that participate in the trial will be provided with multispecies and mixed infection-detecting RDTs, artemether-lumefantrine (AL) and chloroquine obtained from the Oromia Regional Health Bureau (ORHB). The RDT that will be provided is the CareStart® Malaria *Pf/Pv* combo test (Access Bio, Inc., Somerset, NJ, USA), which is individually packaged with an alcohol swab, lancet, capillary tube, buffer and test device.

Through weekly household visits, study participants with a fever or having a history of fever within the past 48 hours, will be encouraged to present to the health posts. Residents will be advised to visit the health posts whenever they develop a fever. They will be asked to show a household card whenever visiting a health post. For individuals without a household card, health workers will use other information that allows them to locate the household and its number. Individuals who are found to be positive for *P. falciparum* by RDT will be given AL twice a day for 3 days based on body weight according to national guidelines [31]. AL is a fixed dose combination of 20 mg artemether plus 120 mg of lumefantrine. *P. vivax* positive individuals will be treated with chloroquine, 25 mg/kg for 3 days (10 mg base per kg on days 1 and 2, and 5 mg base per kg on day 3). Treatment of other conditions will be done in accordance with the national guidelines or a referral to higher level health facilities. Patients with severe illness at the time of visit (from malaria or other causes) will be referred to the nearest health facility. Any person from the study villages treated for malaria at a health center or hospital will also be included in the study.

Thin films of blood slides will be fixed with methanol for 30 seconds. Both thin and thick films will be stained with 3 % Giemsa for 20–30 minutes by experienced laboratory technicians in accordance with the standard malaria laboratory procedures. A thick blood smear will be declared negative with a minimum of 100 high power fields by microscopic examination, while the thin film will be examined to identify the *Plasmodium* species for positive slides. A second reading for all positive and negative slides will be performed by an experienced laboratory technologist and any discordant results will be resolved by a third reader. All blood slide readers will be blinded to the different arms of the trial and to the diagnosis of preceding readers.

At the end of the main malaria transmission season each year, the Hb concentration will be assessed in children 6–59 months old for assessing the prevalence of anemia using a portable photometer (HaemoCue®, Ångelholm, Sweden) in the field. Through house-to-house visits, a single finger-prick sample will be taken from each child, and children’s height and weight will also be measured. A Hb cut-off point of less than 11.0 g/dl will be used to decide whether a child has anemia, and will be further classified into mild, moderate and severe anemia.

Community-based malaria prevalence surveys will be conducted on a representative sample of households from each arm of the trial during the main transmission season (September to November) each year among all age groups. All household members will be eligible to be included in the study. Allowing for ineligible households, absence on the day of the survey and refusals at the household and individual level, approximately 5500 individuals from 1100 households will be estimated to be included in the study. This would provide an average 275 households from each arm of the trial to be included in the study. The households will be randomly selected from the total list of households in all arms of the trial. The heads of the households or their representatives will be interviewed using a pre-tested structured questionnaire. Voluntary individuals will be tested for malaria parasites using RDTs. Moreover, blood slides will also be collected for microscopic examination.

#### Economic evaluation data collections

Costing will be done based on the cost of the interventions from a health systems perspective, with cost data collected by interviewing individual malaria patients, family members and the DHO personnel. The main cost outcome measure will be the total costs of interventions, including all resources used to deliver the interventions and recurrent costs such as personnel, supplies and materials, the operation and maintenance of buildings, utilities and communication costs, in addition to capital costs such as buildings, equipment, and vehicles. The costing of the intervention will be done from the provider’s perspective using a standard malaria costing tool developed by the WHO [57]. The economic evaluation of health outcomes will be evaluated by the number of malaria cases averted and DALYs gained as a result of the interventions using incidence data. The number of deaths averted due to the interventions will be calculated based on the case fatality rates of malaria.

Economic evaluation, cost-effectiveness/utility analysis, presenting cost per malaria case prevented and costs per DALY averted will all be employed. The DALYs will incorporate both morbidity estimates from malaria episodes and anemia among children. We will develop a Markov life cycle model to account for the recurrent nature of malaria disease, with a varying amount of risk for repeated episodes during different seasons of the year. The cost of illness study will be conducted in the same district from non-trial villages to account for saved disease treatment costs. Epidemiological and effectiveness parameters will be based on the findings of this research project, while the clinical course of the diseases will be based on a review of the best available literature. Standard DALY weights will be utilized. Moreover, this trial will incorporate an evaluation of the distributional impact of the interventions using inequality analysis techniques and a decomposition of the inequality into various socioeconomic factors using an extended cost-effectiveness analysis (ECEA). In the ECEA, we will estimate the benefit of the interventions across different levels of income group in terms of the number of deaths prevented, the net financial risk protection provided, the out-of-pocket expenditure averted and the number of poverty cases prevented.

#### Entomological data collections

The results of trials from countries where *An. gambiae* s.s. is the dominant vector might not be fully applicable in countries such as Ethiopia, where *An. arabiensis* is the main vector. The latter vector is less affected by mosquito nets, and is more exophilic and less anthropophilic [58]. Estimating the human biting rate (HBR) of mosquitoes is important for a risk assessment of malaria transmission. The Centers for Disease Control and Prevention (CDC) light traps, used in many studies, are only a proxy measure to estimate HBR. Human landing catches (HLC) are a more direct way to estimate HBR, and are often considered the “gold standard” [59]. Recent research showed that light trap collections placed close to inhabited mosquito nets may not be a reliable method of assessing human biting rates [60].

The CDC light traps and HLC will be compared before starting the trial. Since HLC cannot be used for community-wide mosquito collections due to ethical and logistical drawbacks, CDC light trap collections will be calibrated with HLC locally in order to estimate an operational conversion factor for calculating the HBR and EIRs. Mosquito collections will be carried out during the malaria transmission season following interventions.

The CDC light traps, pyrethrum spray sheet catches and artificial pit shelters will be employed to collect mosquitoes and assess their biting behavior, indoor and outdoor resting densities. Houses will be randomly selected from a computer-generated list and the person will be blinded to the arms and houses. For CDC light traps and pyrethrum spray catches, the number of houses will be four and 16 from each arm, respectively, while four pit shelters in each arm will be constructed. Mosquitoes will be collected weekly from August to November each year, and will be identified to species using a morphological key [61]. Previous studies indicated the presence of *An. arabiensis* as the only species of the *An. gambiae* complex in the study area [50]; however, for reconfirmation purpose a species-specific polymerase chain reaction (PCR) will be applied [62].

From all collections, blood-engorged female mosquitoes will be analyzed using Enzyme- linked Immunosorbent Assays (ELISAs) for determining the blood meal source of vectors in indoor or outdoor situations [63]. All collections of female anophelines, with the exception of blood-fed mosquitoes, will be subjected to a sporozoite test by employing ELISA [64] and a parity determination by ovary dissection [65].

Insecticide resistance in *An. arabiensis* and *An. pharoensis* will be monitored annually throughout the study period using standard WHO tube tests [66]. The insecticides will be the pyrethroids (deltamethrin, alphacypermethrin, permethrin and lambdacyhalothrin) and the carbamates (bendiocarb and propoxur). In order to assess any change in resistance, the resistance intensity will be quantified. For the insecticide susceptibility tests, larvae and pupae of the two species will be collected from breeding habitats and reared to adults. The status of physiological susceptibility/resistance of females will then be determined. Molecular [67] and biochemical analyses [68] will be used to identify potential insecticide resistance mechanisms. Sporozoite rates will be determined by ELISA and rechecked by real-time PCR [69]. The decay rate of propoxur will also be assessed monthly by conducting cone wall bioassays on eight randomly selected houses from the two arms (IRS and LLINs + IRS) [70] for a period of at least 6 months post spraying. An insectary colony of *An. arabiensis* (Debre Zeit strain, being maintained at the Aklilu Lemma Institute of Pathobiology, Addis Ababa University since 2001), which is susceptible to all insecticides including propoxur, will be used for the bioassay test.

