### Study endpoints

The primary health outcome measure is malaria incidence determined by the detection of *P. falciparum* or *P. vivax* by rapid diagnostic tests (RDTs) in patients with a fever or having a history of fever within the previous 48 hours upon arrival at health posts by passive case detection (PCD). The sensitivity and specificity of the RDTs compared with the results of the light microscopy will be determined. The secondary health outcome measure is mean Hb concentration in children under the age of 5 years, which is measured using a portable photometer (HaemoCue®, Ångelholm, Sweden) at the end of each transmission season through community-based house-to-house visits.

The primary outcome measure of the economic evaluation is the total cost of the interventions. The secondary outcome measures are the direct and indirect costs of the intervention from both the provider and societal perspectives, which includes Disability- adjusted Life Years (DALYs) and the number of malaria cases averted by each intervention.

The primary entomological outcome measure is malaria transmission expressed as EIR, estimated as the mean number of sporozoite infective bites/person/year. The secondary entomological outcome measures are the mean number of *An. arabiensis*/light trap/night, and mean number of *An. arabiensis* in spray catches/night inside houses.

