#### Entomological study

We aim to calculate the sample size for the entomological collections based on the pilot entomological studies. In a West African study with a 90 % power and 5 % significance level, it was advised to sample eight houses from each of 15 clusters of the study arms, but the mosquito density was lower [56]. A total of 16 villages (four per arm) will be randomly selected for entomological study, in which indoor host-seeking mosquitoes will be collected by CDC light traps from four houses per arm, indoor resting mosquitoes from 16 houses per arm using pyrethrum spray collection and outdoor resting mosquitoes from four artificial pit shelters per arm of the study.

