#### Adverse events and malaria treatment

We do not anticipate any physical harm or risks to the participants. Blood samples for RDTs, microscopic examination of slides and Hb measurements will be collected using aseptically disposable lancets. A finger-prick for blood sample collection may result in mild pain and bruising at the site where blood is obtained, but will not cause any further harm. The collection of blood samples from finger-pricks is part of the routine procedures in the diagnosis of malaria by health workers. Malaria treatment will be provided according to the national guidelines using AL and chloroquine, which are the first-line antimalarial treatments for *P. falciparum* and *P. vivax*, respectively [43]. All study participants visiting health posts will be examined and treated for malaria free of charge, while the mass distribution of LLINs and IRS spraying will be carried out by the *MalTrials* project for free in collaboration with the DHO. Mosquito collectors will be trained to collect mosquitoes as soon the mosquitoes land and before they bite. To help minimize risk, data collectors will be provided with an appropriate prophylactic drug (Malarone) before the collections.

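### Females that are blood-fed when caught get no sporozoite test, so the sporozoite rate and the EIR rest on a subset; this loses specimens and may bias the arm comparison

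*Protocol article*

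**What the plan says.** The rule is in the protocol article under Entomological data collections: "All collections of female anophelines, with the exception of blood-fed mosquitoes, will be subjected to a sporozoite test by employing ELISA". The same sentence applies the exclusion to parity dissection. Fed females from every collection method go to a different assay: "blood-engorged female mosquitoes will be analyzed using Enzyme- linked Immunosorbent Assays (ELISAs) for determining the blood meal source of vectors in indoor or outdoor situations". The section later adds: "Sporozoite rates will be determined by ELISA and rechecked by real-time PCR". That sentence confirms the ELISA result and does not bring fed females back in.

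Two outcomes depend on this test. Study endpoints states: "The primary entomological outcome measure is malaria transmission expressed as EIR, estimated as the mean number of sporozoite infective bites/person/year". The secondary objectives also list the sporozoite rate as a parameter to be compared between the combined arm and each single-intervention arm.

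The biting component of the EIR has its own source: "CDC light trap collections will be calibrated with HLC locally in order to estimate an operational conversion factor for calculating the HBR and EIRs". No exclusion of fed females is stated for that count. Under Sample size, the entomological study is limited to four villages per arm. There, "indoor host-seeking mosquitoes will be collected by CDC light traps from four houses per arm", and "indoor resting mosquitoes from 16 houses per arm using pyrethrum spray collection", with four pit shelters per arm for outdoor resting mosquitoes.

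**The concern.** The EIR is a biting rate multiplied by a sporozoite rate. As written, the two factors describe different groups: the biting factor counts light-trap females with no stated restriction, while the sporozoite factor covers only those not fed at capture.

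Two things are at stake. The first is precision: females already caught and identified contribute nothing to the sporozoite rate, in a sub-study with few villages and houses. The second is comparability. Whether a mosquito is fed when caught is a state observed after randomization, and nets and indoor spraying may plausibly change it. A rate computed within a subset chosen on such a state no longer has the full protection of randomization.

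**Working it through.** The article gives no sporozoite rate, blood-fed share, catch size or EIR, so there is no figure of its own to reproduce. What follows is a sensitivity check on assumed values.

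**Notation.** f is the share of caught females that are blood-fed. r is the sporozoite rate in fed females divided by the rate in unfed females. Subscript 1 is the combined arm and subscript 0 a comparator. The reference is the rate over all females of the same collection. Here, unfed means every female not classed as blood-fed at capture.

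**Step 1: precision.** If N females are caught, (1 − f)N are tested. With simple binomial sampling and a similar rate in both groups, the confidence interval widens by 1/√(1 − f).

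| f (assumed) | Widening |
|---|---|
| 0.05 | 1/√0.95 = 1.03 |
| 0.30 | 1/√0.70 = 1.20 |
| 0.50 | 1/√0.50 = 1.41 |
| 0.80 | 1/√0.20 = 2.24 |

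Variation between villages, which more specimens do not reduce, would make the widening smaller than this.

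**Step 2: level within one arm.** The planned rate divided by the all-female rate is 1/(f·r + 1 − f).

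| r (assumed) | f = 0.05 | f = 0.30 | f = 0.50 | f = 0.80 |
|---|---|---|---|---|
| 0.5 | 1.03 | 1.18 | 1.33 | 1.67 |
| 1 | 1.00 | 1.00 | 1.00 | 1.00 |
| 2 | 0.95 | 0.77 | 0.67 | 0.56 |

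**Step 3: comparison between arms.** The exclusion multiplies the between-arm ratio of sporozoite rates, and so the EIR ratio, by (f₀·r + 1 − f₀)/(f₁·r + 1 − f₁). For example, with f₁ = 0.10, f₀ = 0.30 and r = 2, this is 1.30/1.10 = 1.18.

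| f₁ / f₀ (assumed) | r = 0.5 | r = 1 | r = 2 | r = 3 |
|---|---|---|---|---|
| 0.05 / 0.10 | 0.97 | 1.00 | 1.05 | 1.09 |
| 0.10 / 0.30 | 0.90 | 1.00 | 1.18 | 1.33 |
| 0.30 / 0.80 | 0.71 | 1.00 | 1.38 | 1.63 |
| equal shares | 1.00 | 1.00 | 1.00 | 1.00 |

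The multiplier is exactly 1 when r = 1 or when the fed shares are equal. Otherwise it can lie on either side of 1. If all females of the collection were tested, it would be 1 by construction.

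**The case against.** The strongest reply concerns what the EIR measures. Its biting factor comes from host-seeking females in light traps, calibrated to human landing catches. Of the landing catches the article says: "Mosquito collectors will be trained to collect mosquitoes as soon the mosquitoes land and before they bite". A reader might infer that the EIR leaves out the females that actually bit. The article does not support that: no bite is dropped from the count, and a female unfed at capture may have fed earlier. What is missing is the infection status of females that were fed when caught. A resting fed female may also have fed on an animal, and the article describes the main vector as less inclined to bite people. A sporozoite rate pooled across resting and light-trap catches would therefore be a poor multiplier for a light-trap biting rate. This part of the reply stands and shapes the fix.

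A reader might also infer that the excluded share differs by arm. The article has no data on this; it is plausible but assumed.

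Nor does a constructed example prove bias. Take 1.2% infected among fed and 0.6% among unfed females in both arms, with fed shares of 50% and 25%. The all-female rates are 0.90% and 0.75%, a ratio of 0.83, against 1.00 among unfed females. Since infection does not differ between arms within either group, the example shows only that the pooled rate responds to the fed/unfed mix.

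Finally, assay allocation could be seen as laboratory detail that an article leaves to operating procedures. That would excuse silence, but here the article states an explicit exclusion covering all collections. It is true that the article does not say which collection supplies the EIR sporozoite rate or how partly digested or gravid females are classed. The number of tests lost therefore cannot be fixed from it.

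**Conclusion.** The point holds in a limited form. It is certain that specimens from females fed at capture are withheld from the test behind the sporozoite rate and the EIR, with no reason or adjustment given. The size of the loss depends on the fed share: little at 5%, and an interval about 1.2 to 2.2 times as wide at 30% to 80%, under the binomial assumption.

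Bias between arms is possible but not shown. It needs both unequal fed shares and different infection rates in fed and unfed females. Over the assumed values with unequal shares and r different from 1, the multiplier on the EIR ratio runs from 0.71 to 1.63, with no known direction. If the EIR uses light-trap females only and few of those are fed, the effect would be near the small end (0.97 to 1.09 in the first row of the last table).

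The issue is confined to the entomological sub-study. Malaria incidence by rapid test, the primary health outcome, is unaffected. The change is still worth making because the loss is avoidable with an assay already planned.

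**What to change.** Amend Entomological data collections so that all female anophelines, including blood-fed ones, receive the planned sporozoite ELISA with its PCR recheck. Blood-fed females keep the blood-meal ELISA as well, and parity dissection can remain restricted to those not fed. How one specimen serves both assays belongs in the laboratory procedures.

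Report sporozoite rates, numbers tested and fed shares by arm and collection method. For the EIR, multiply the light-trap biting rate by the sporozoite rate of all light-trap females, not by a rate pooled across methods.

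The cost is additional ELISA reagents and bench time on specimens already collected; no new field collection is needed. Table 1 schedules laboratory assays and field surveys through every month of 2016, so the change could still be made after the article's January 2016 publication. Whether fed specimens from earlier seasons were kept in a testable state is not stated. If they were not, earlier seasons should be reported separately, with the exclusion named.
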